### Analysis Plan

The analysis of quantitative study data will be conducted using STATA and R (R Foundation), where appropriate. Descriptive analysis will be performed for all variables, and unadjusted comparisons between experimental arms will be conducted. Descriptive statistics, including frequencies, means, and SDs, will also be performed. Chi-square tests and one-tailed *t* tests will be used to examine associations in the data. A probability value of less than .05 will be considered statistically significant for all the statistical tests that are conducted. Continuous variables will be tested for normality, and nonnormal values will be categorized or appropriately transformed. Given our hypotheses regarding the impact of our intervention on our key outcomes, one-sided hypothesis tests will be conducted for all our main analyses.

Our main econometric specifications will (1) estimate the intent-to-treat (ITT) effects of our family planning intervention on fertility intentions and preferences, contraceptive intentions and preferences, intention to switch methods, and other outcomes related to contraceptive behaviors by directly regressing our outcomes of interest on a binary variable indicating receipt of the intervention and (2) estimate the effect of interventions on downstream behavioral outcomes (such as women’s uptake of contraceptive options and the concordance between their revealed preference and their stated preference) using a 2-stage least squares model, in which the intermediate counseling variable will be instrumented by the treatment. The main econometric specification for estimating the ITT effect of our family planning intervention is defined as follows:

*Y_it_* = *β_0_* + *β_1_T_it_* + *X_it_ζ* + *Y_i0_* + *η_i_* + *ε_it_*

where *Y_it_* is the outcome variable of interest for woman 𝑖 in time period 𝑡=0, 1, 2 for baseline (time period 0) and follow-up (time periods 1 and 2), respectively; *T_it_* is an indicator of assignment to 1 of the 3 treatment arms; *X_it_* is a vector of individual-level covariates that are controlled for in the analysis; η_i_ is the individual-specific fixed effect; *Y_i0_* is the baseline level of the outcome; and *ε_it_* is the error term. Here, the outcome variables of interest include immediate, intermediate, and long-term outcomes described in the previous sections.

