#### Contraceptive Prevalence: Partner Invitation Interventions

Using modern contraceptive prevalence estimates for urban area of Malawi from the 2010 Malawi DHS, we assume a modern contraceptive prevalence rate of 50% among women aged 18-35 years who are currently not pregnant and who did not give birth in the 6 months before the baseline. To infer a potential effect size for our intervention, we look to evidence to a study from Zambia [28], which found that male involvement in family planning care-seeking decreased the probability of receiving family planning services by 19% over a 2-year study period. Our study differs from this study in that we do not require husbands to participate in the counseling session; instead, we leave it up to the woman to decide whether she would like to invite her husband to counseling or not. In designing our invitation in this way, a selection effect might exist, in which husbands who are more supportive of contraceptive use are more likely to comply with the intervention and participate in a joint counseling session. As a result, our male partner invitation intervention would likely lead to an increase in contraceptive prevalence.

Assuming an attrition-adjusted sample of 700 women, with 400 women assigned to partner invitation arms, T1 and T3, compared with 300 women assigned to noninvitation arms, T0 and T2, we will have 75% power to detect a percentage point increase of 10 in the contraceptive prevalence rate from 50% to 60% (α=.05, two-sided). If, instead, we use a one-sided test, then we estimate that we would have 85% power to detect the same 10 percentage point increase in contraceptive prevalence.

Table 4 presents the levels of power (1−β) that could be achieved for various minimum effect sizes for the modern contraceptive prevalence use, assuming a baseline contraceptive prevalence rate of 50% in both the intervention and control arms and a fixed endline sample size of 700 women.

**Table 4 table4:** Power calculations for contraceptive prevalence rate, partner invitation intervention.

Control CPR^a^, n (%)	Intervention CPR, n (%)	Significance level, α	Control sample size, n	Intervention sample size, n	Power
150 (50)	236 (59)	.05	300	400	0.66
150 (50)	240 (60)	.05	300	400	0.75
150 (50)	244 (61)	.05	300	400	0.83
150 (50)	248 (62)	.05	300	400	0.89

^a^CPR: contraceptive prevalence rate.

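### The main ITT regressor is defined once as receipt of the intervention and once as assignment; only assignment gives an ITT analysis, and the receipt wording should go

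*Protocol article*

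**What the plan says.** The Analysis Plan names two main specifications. The first estimates ITT effects by "directly regressing our outcomes of interest on a binary variable indicating receipt of the intervention". The second is a two-stage least squares model "in which the intermediate counseling variable will be instrumented by the treatment".

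The equation printed next is introduced as the main ITT specification. In its legend, T_it "is an indicator of assignment to 1 of the 3 treatment arms", η_i "is the individual-specific fixed effect" and Y_i0 "is the baseline level of the outcome".

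On testing, the same section says that "one-sided hypothesis tests will be conducted for all our main analyses", and sets the threshold: "A probability value of less than .05 will be considered statistically significant for all the statistical tests that are conducted".

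Three other places bear on the point:
- Under Randomization, a woman in T1 or T3 brings her husband only if she chooses to. Under Informed Consent and Participant Privacy, any component of the intervention may be declined or stopped.
- The power subsection on contraceptive prevalence for partner invitation says that a selection effect might exist, in which "husbands who are more supportive of contraceptive use are more likely to comply with the intervention".
- All the power calculations compare women by assigned arm, 400 against 300.

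**The concern.** Receipt and assignment are different variables whenever an assigned woman does not take up what she was offered. In T1 and T3 this can happen by design. If receipt is taken to mean that the husband attended, invited women whose husbands stayed away join the comparison group and the randomised comparison is lost.

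The coefficient would then mix any effect of the invitation with the husband's prior support for contraception, while still being labelled ITT. For contraceptive use, the selection that the protocol describes points upward, which is the direction in which a one-sided test for an increase would count it as success. The introduction criticises earlier work on male involvement because counseled couples were self-selected; a receipt regression would bring that selection back.

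**Working it through.** **1. The plan's own figure.** For prevalence of 50% v 60% with 300 v 400 women, the pooled proportion is (150 + 240)/700 = 0.557.
- Null SE = √[0.557 × 0.443 × (1/300 + 1/400)] = 0.0379. Alternative SE = √(0.25/300 + 0.24/400) = 0.0379.
- Two-sided power = Φ[(0.10 − 1.960 × 0.0379)/0.0379] = 75.1% (stated 75%).
- One-sided power = Φ[(0.10 − 1.645 × 0.0379)/0.0379] = 84.0% (stated 85%).

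So the power section describes an analysis by assignment.

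**2. Receipt regression with no true effect, unadjusted, set-up A.** The documents give neither attendance nor the prevalence gap, so the following are assumptions: half of husbands are supportive; attendance is 50% if supportive and 20% if not; use is 60% v 40% by support.
- Attendance among invited couples = 0.5 × 0.5 + 0.5 × 0.2 = 35%, so 400 × 0.35 = 140 women count as receivers and 560 do not.
- Supportive share among attenders = 0.25/0.35 = 71.4%. Use among receivers = 0.714 × 60% + 0.286 × 40% = 54.3%.
- Use among the rest = (350 − 140 × 0.543)/560 = 48.9%.
- Spurious difference = 5.4 points. SE = √[0.25 × (1/140 + 1/560)] = 4.7 points.
- One-sided rejection at .05 is about 30% (31% by simulation).
- Range: use 55% v 45% gives 2.7 points and 14%; use 65% v 35% gives 8.0 points and 52%.

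**3. The same check, set-up B.** Let u be the share of invited couples who attend and g the prevalence gap between attending-type and other couples, with overall use at 50%. Receivers number 400u with use 0.5 + g(1 − u). The rest are 300 women at 0.5 plus 400(1 − u) women at 0.5 − gu.
- u = 50%, g = 10 points: 55% v (150 + 90)/500 = 48%, a spurious 7.0 points; rejection 51%.
- g = 10 points with u = 30% or 70%: 8.4 or 5.0 points; rejection 52% or 36%.
- u = 50% with g = 5 or 20 points: rejection 21% or 96%.
- g = 0, or u = 100%: no bias; rejection 5%.

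**4. Adding the terms in the printed model.** This is a two-wave simulation; the plan has three time points. It uses set-up B with u = 50%, g = 10 points, no true effect, and an assumed 60% of women keeping their baseline status. One-sided rejection:

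| Extra change over time in attending-type couples | Receipt, unadjusted | Receipt, baseline-adjusted | Receipt, fixed effect | Assignment |
|---|---|---|---|---|
| none | 51% | 21% | 5% | about 5% |
| 5 points | 80% | 59% | 25% | about 5% |
| 10 points | 95% | 90% | 59% | about 5% |

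Set-up A with a baseline wave added behaves the same way when the gap is constant. Baseline adjustment gives 30%, 14% and 10% when 0%, 60% and 80% of women keep their baseline status, and the fixed effect gives about 5% in all three. In the 65% v 35% case the fixed effect also brings the 52% down to about 5%.

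**5. Which adjustment applies.** The equation prints both Y_i0 and an individual fixed effect. Y_i0 does not vary over time within a woman, so a fixed effect would absorb it. The text does not settle which of the two would be in force.

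**The case against.** The best reply is that receipt is loose wording and assignment was meant. Much supports this. The sentence itself calls the estimand ITT, the formal equation defines T_it by assignment, the two-stage step makes sense only if treatment means assignment, and every power calculation is by assigned arm. The section also never says that receipt means the husband's attendance. If the intervention is the encouragement to invite him, receipt and assignment nearly coincide. All of this stands as evidence of intent. It does not remove the conflicting sentence, and it argues for correcting it.

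A reader might go further and infer that the receipt version will produce a false-positive effect of husband invitation. The documents do not support that:
- No attendance rate or prevalence gap is reported, and the protocol says only that selection might exist.
- With full attendance or no gap there is no bias.
- The 14% to 52% comes from an unadjusted test. Under the printed fixed effect, a constant gap leaves the error rate at about 5%.
- The upward direction is documented only for contraceptive use. Uptake is named under the two-stage model; the ITT sentence names intentions, preferences and intention to switch, and only generally other contraceptive behaviours. For intention to switch, the protocol says that male involvement could work either way.

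The fixed effect is not a complete answer either. It protects only against a gap that stays constant. All arms are offered free transport and reimbursement, so use could rise more where husbands are supportive. That is plausible but not stated in the protocol.

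**Conclusion.** The contradiction is real and concerns the definition of the main analysis. One of the two definitions is not ITT. The text around it favours assignment without settling the matter.

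The consequence is conditional. If receipt is read as the husband's attendance, the invitation effect on contraceptive use can be biased upward, by an amount the documents do not allow anyone to calculate. Under the assumed values, one-sided rejection with no true effect is about 14% to 52% unadjusted. It is generally lower with baseline adjustment. With the individual fixed effect it is about 5% if the gap is constant, and 25% to 59% if attending couples have a 5- to 10-point larger change. Assignment holds about 5% in every scenario and does not depend on any of these assumptions. The case for the change rests on the contradiction, not on any one of these rates.

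**What to change.** In the Analysis Plan, replace the phrase about a binary variable for receipt with indicators of random assignment, so that the sentence agrees with the T_it legend and the power section. State that every randomised woman is analysed in her assigned arm, whether or not the husband attended or the session took place. Leave receipt to the two-stage least squares analysis, and label any direct regression on receipt as non-ITT.

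The cost is one phrase and a clarifying sentence. No data or sample size changes, and planned power stays as in step 1 of the working (75.1% two-sided, 84.0% one-sided for 50% v 60%). The article reports the primary analysis as still ongoing, so the definition can be fixed before results are reported.

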
### Study Objectives

In this study, we identified the causal impact of user-centered approaches to family planning counseling on women’s contraceptive preferences and decision making by means of a randomized controlled trial. In particular, we investigated two channels that have been hypothesized to play a role in contraceptive decision making: (1) a preference-based, targeted, user-centered approach to family planning counseling and (2) male involvement in family planning counseling. To this end, we tested the following 2 hypotheses:

A preference-driven, tailored, user-centered approach to counseling would allow women to express and realize their contraceptive preferences more effectively.The involvement of male partners in family planning counseling may allow women to express their contraceptive preferences and, in turn, translate their preferences into behavior more effectively.

The study population comprised married women aged 18-35 years living in Lilongwe, Malawi. As part of the trial, each woman in the study was randomly assigned to 1 of the 3 treatment arms or a control arm. A woman assigned to one of the intervention arms received one tailored, user-centered counseling session, followed by a package of family planning services that was designed to reduce the key barriers to accessing family planning in urban Malawi. The primary objective of this study is to evaluate the impact of user-centered counseling on a woman’s contraceptive use, intention to change stated ideal methods, switching of the current method, and realization of the stated ideal method. Primary outcomes include changes to women’s contraceptive method preferences (both stated and realized) over time and changes to women’s contraceptive concordance (whether a woman’s stated choice of contraceptive method, her ideal method, is the method that she is, in fact, using). Secondary outcomes include changes to male partners’ fertility and family planning preferences, women’s sexual and marital well-being, and changes in women’s decision-making in the household.

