### The Intervention

#### Intervention Protocols

All women who consented to participate in the study (T0-T3) were offered a free, private family planning counseling session, which included a risk assessment for contraceptive methods and detailed information on methods switching, side effects associated with each method, and the benefits of contraception and birth spacing. A precounseling survey was administered to each woman, where they were asked to confirm their personal information, including, but not limited to, pregnancy status, current contraceptive use, and preferences for fertility and contraception. During counseling sessions, counselors provided women with information on the range of modern and natural family planning methods based on their respective intervention assignments. Strategies on how to communicate family planning messages with partners and on how to increase partner awareness were conveyed during the sessions. The counseling session lasted no more than 1 hour and was administered in a private room by a counselor who was trained to provide family planning and reproductive health services. To facilitate an effective and open dialog with women during the counseling session, only female counselors were hired. Counselors were hired by IPA Malawi, held a nursing degree, and were trained on the range of counseling protocols over a week. We enlisted the support of the Malawi RHD and several international nongovernmental organizations who work on family planning, including Population Services International (PSI), BLM, the Family Planning Association of Malawi, and FHI360, to help us develop training materials and counseling resources. We also collaborated with the Malawi RHD, BLM, and PSI to assist with counselor training.

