### Sample Size and Power Calculations

#### Target Sample and Key Outcomes

The sample size of this study was powered to primarily identify the independent effects of tailored family counseling and male involvement on women’s contraceptive uptake and switching of methods. On the basis of the preliminary power calculations for the primary outcomes of interest, our target baseline sample consists of 700 eligible women who consent to participate in the study. Among these 700 women, 100 women were assigned to the control arm T0, and 200 women were assigned to each of the 3 intervention arms, namely, T1, T2, and T3.

Previous studies have found that one-fifth of women of reproductive age were either pregnant or had given birth to a child in the past 6 months [40]. To meet our target sample size of 700 women who would be eligible to participate in our study, we need to recruit a total of 940 women if we conservatively assumed a combined ineligibility or refusal rate of 25%.

We have powered our study to detect effects on the following outcomes: (1) contraceptive uptake and (2) intention to switch from the current contraceptive method.

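### The 2SLS model for uptake and concordance does not identify a counseling effect, because its only defined instrument pools three arms that change two things at once

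*Protocol article*

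**What the plan says.** The Analysis Plan section sets out two main specifications.

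- **Intent-to-treat.** Outcomes on intentions, preferences and other contraceptive behaviors are regressed "on a binary variable indicating receipt of the intervention". In the displayed equation the treatment term has a single coefficient, and T "is an indicator of assignment to 1 of the 3 treatment arms". The text below the equation says that it serves immediate, intermediate and long-term outcomes.
- **2SLS.** Downstream behavioral outcomes, "such as women’s uptake of contraceptive options and the concordance between their revealed preference and their stated preference", are estimated by 2-stage least squares, "in which the intermediate counseling variable will be instrumented by the treatment".

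Three other sections bear on this.

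- Intervention Protocols: "All women who consented to participate in the study (T0-T3) were offered a free, private family planning counseling session".
- Study Objectives: "we investigated two channels that have been hypothesized to play a role in contraceptive decision making". They are targeted counseling and male involvement. The same section puts concordance among the primary outcomes.
- Target Sample and Key Outcomes: "We have powered our study to detect effects on the following outcomes: (1) contraceptive uptake", with intention to switch as the second. The power sections compare 400 with 300 women separately for each factor: T1+T3 against T0+T2, and T2+T3 against T0+T1.

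**The concern.** An instrument must move the endogenous variable (relevance) and must affect the outcome only through that variable (exclusion). Here the instrument is the treatment, defined only as membership of any intervention arm, and the design gives that indicator two routes to uptake. Two-thirds of the intervention women are shown fewer methods and two-thirds are encouraged to bring a husband, while the control arm gets neither. A single counseling variable cannot carry both routes.

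Uptake is a powered outcome and concordance a primary one. A coefficient reported as the effect of counseling, or of husband attendance, could in fact be the effect of the other factor divided by an attendance rate. The trial is meant to separate the two factors, and this model merges them.

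**Working it through.** **1. The plan's own figures.** For 300 against 400 women and 50% against 60%, the normal-approximation power is 0.751 two-sided (stated 75%) and 0.840 one-sided (stated 85%). For 20% against 30% it is 0.856 (stated 86%) and 0.917 (stated 92%). All rows of Tables 4 to 7 reproduce. These are comparisons by assigned factor; no power is stated for 2SLS.

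**2. Inputs for the 2SLS check.**

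- From the protocol: planned arms T0/T1/T2/T3 = 100/200/200/200; all arms offered counseling; husband invitation encouraged but not compelled.
- Assumed, because the protocol gives no figures: session take-up of 90%, equal in all arms; attendance h among counseled invited husbands of 20% to 80%; no attendance without invitation; effects a (targeting) and b (husband attendance) that add.

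With one binary instrument, the 2SLS estimate is the intent-to-treat difference divided by the first stage.

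**3. Pooled instrument, 600 against 100, under each reading of the counseling variable.**

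- *Session received.* First stage = 0.90 − 0.90 = 0, so the ratio is undefined.
- *Husband attended, true effect 0, targeting effect a.* Intent-to-treat difference = (400/600) × 0.9 × a. First stage = (400/600) × 0.9 × h. The ratio is a/h. With a = 3 points: 1.8/0.30 = 6 points at h = 50%, and 1.8/0.18 = 10 points at h = 30%. With a = 10 points: 50, 20 and 12.5 points at h = 20%, 50% and 80%.
- *Targeted content received, true effect 0, husband effect b.* Intent-to-treat difference = (400/600) × 0.9 × h × b. First stage = (400/600) × 0.9 = 0.60. The ratio is h × b. With b = 10 points: 2, 5 and 8 points at h = 20%, 50% and 80%.
- *Post-counseling stated preference.* No arithmetic is needed. The Study Limitations section expects the partner to influence the choice that a woman finally realizes. That is a path to uptake that bypasses her stated preference.

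**4. Factor-specific instruments.**

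- *Invite alone, Targeted not in the model.* The 2:2:2:1 allocation leaves the targeted share at 200/400 = 50% among invited women and 200/300 = 66.7% among the others. The bias for husband attendance is (0.500 − 0.667) × a/h. With a = 3 points this is about −1.0 at h = 50% and −1.7 at h = 30%: smaller, and of opposite sign.
- *Other factor held fixed* (T1 against T0 for attendance, T2 against T0 for targeted content). The true value is recovered in every scenario tried under the additive model.

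**5. The intent-to-treat equation as displayed.** With T pooled, the contrast is 600 against 100. Power for 50% against 60% is then 0.468 two-sided (0.592 one-sided), and for 20% against 30% it is 0.539 (0.673). This contrast estimates neither factor's effect separately.

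**6. Power of a two-factor model.** The correlation of the Invite and Targeted indicators is (200/700 − (400/700)²) / ((400/700)(300/700)) = −0.0408/0.2449 = −1/6. The variance inflation is 1/(1 − 1/36) = 1.029, so standard errors rise by about 1.4%. For 50% against 60%: (1.960 + 0.678)/1.014 − 1.960 = 0.64, or about 74% power against the stated 75%.

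**The case against.** **The endogenous variable is undefined, and a fuller plan may define it.** This stands as far as it goes: a missing definition in an article is not a fault. The fault is in what is stated, namely one counseling variable and one pooled treatment indicator. That pairing fails for each reading checked.

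**The treatment might mean arm-specific or factor-specific assignment.** If so, 2SLS can be sound. A reader might infer that instrumenting is invalid under any reading, or that 2SLS for targeted counseling must be ruled out. The protocol does not support either inference. Assignment is randomized and husband attendance is voluntary, so a factor-specific instrument with the other factor in the model is a legitimate non-compliance analysis if its exclusion assumption holds. Counseling in all arms defeats only the session-receipt reading.

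**Uptake and concordance also get an intent-to-treat analysis.** This is correct, so a randomized comparison is not excluded. But the equation carries the same pooled indicator, and nothing says which result governs if the two disagree.

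**The size of the bias is assumed.** It is. Neither a 3-point effect nor 30% to 50% attendance comes from the protocol, and the 6 to 10 points apply only to the pooled instrument.

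**2SLS inflates the standard error.** A reader might take this as lost power. In a just-identified model the estimate and its standard error both scale by about one over the first stage, so the test of no effect is essentially the intent-to-treat test. No power loss follows from this alone, and the stated power figures for the assignment contrasts are unaffected.

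**Conclusion.** The point holds for the specification as written. With T a single indicator for any intervention arm, 2SLS has no first stage for session receipt if take-up is equal across arms. For husband attendance or targeted content it violates exclusion, because the other factor also moves the outcome. Under the assumptions in the working, the spurious attendance effect is a/h: 6 to 10 points for a 3-point targeting effect at 50% to 30% attendance. That compares with the 10-point difference for which the trial was powered. The spurious effect for targeted content is smaller, h × b. The direction and size in this trial depend on effects and attendance rates that the protocol does not report.

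The conclusion does not extend to every instrumental-variable analysis of these data. It should be put right before the behavioral results are reported.

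**What to change.** 1. Name as confirmatory for uptake and concordance an intent-to-treat model with separate Invite (T1, T3) and Targeted (T2, T3) indicators and the randomization strata. This matches the factor contrasts in the power sections. Having both factors in the model removes the 50% against 66.7% imbalance, at a cost of about one point of power.
2. State that this model takes precedence over 2SLS for those outcomes.
3. Keep 2SLS as secondary or exploratory. Instrument husband attendance by Invite and, if wanted, receipt of targeted content by Targeted, always with the other factor and the strata in the model.
4. Report first-stage strength and state the exclusion assumption. For Invite, note that the invitation alone may prompt discussion at home; a direct effect d of that kind adds about d/h to the estimate.
5. Do not use the pooled indicator as an instrument, and do not use post-counseling stated preference as the instrumented variable.

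The cost is analysis-plan wording and rerunning models on data already collected. The protocol describes the analysis of primary outcomes as ongoing. No design change or new data are needed.
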